### Data monitoring

For the trial, no data monitoring committee is needed because all interventions are conducted by skilled and trained instructors, and no instructor has an interest in the specific outcomes of any intervention. Furthermore, the leading project staff will observe the participants. If any sign of indisposition, pain, dizziness, or states of confusion appear during measurements at any point, the project staff will intervene and stop the procedure or intervention. If any participant has a significant event (e.g., a fall) that could affect their participation in the study, the nursing home staff will inform the project staff and offer documentation and interpretation of the results.

## Discussion

This cluster-randomized trial aims to assess the impact of a physical activity-promoting culture, compared to three other interventions, on nursing home residents’ PA behavior and physical functioning. We expect the physical activity-promoting culture, which combines exercise classes and environmental changes, to increase PA, reduce sedentary behavior, and improve physical functioning (Giurgiu et al., 2020; Lopponen et al., 2021) more effectively than either intervention alone or a non-guided environmental intervention. Overall, the PROGRESS study offers a new practical approach to implementing active aging in nursing homes. It aims to encourage the integration of PA programs led by professionally educated instructors into the prevention planning of nursing homes, together with environmental changes that might promote PA behavior in general. The participatory approach enables residents, nursing staff, social services, and relatives to be aware of and incorporate any changes in the residents’ environment. This approach is hypothesized to promote physical functioning and activity, even in challenging situations. A physical activity-promoting culture that is lively, happy, and healthy can only be developed if all individuals who work, live, and visit the nursing home support each other through PA. The findings can provide guidance for addressing current and future challenges in health promotion initiatives in long-term care, which is of great importance in aging societies.

When residents are mobile, able to take care of themselves, and challenged and encouraged in their environment, they might become more physically active (den Ouden et al., 2017). Staying active is believed by many older adults to enrich their overall life experiences (Guell et al., 2016; Halaweh et al., 2018), and data from Sococco et al. shows that only 5.9% of residents move into a nursing home based on their own decision (Scocco et al., 2006). However, the decrease in obligations as well as physical and cognitive limitations that often come along with moving into a nursing home can lead to immobility and dependence on others, as well as an increase in sedentary behavior. As seniors become sedentary and less physically active, their physical and cognitive abilities often decline rapidly (Auerswald et al., 2020). Due to spending most of their time in one place, typically their room (Jansen et al., 2017), their spatial orientation abilities also decrease (Wollesen et al., 2020a), leading to isolation, loneliness, and depression (Antoniewicz and Brand, 2016) and a decline in quality of life (Saajanaho et al., 2016; Duppen et al., 2020). Most studies that have examined the effects of physical exercise on these health outcomes (Fiatarone et al., 1990; Crocker et al., 2013; Johnen and Schott, 2018; Cordes et al., 2019) have revealed that multicomponent training can affect physical and cognitive outcomes, such as walking, balance, dual-tasking abilities, and wellbeing (Wollesen and Voelcker-Rehage, 2014). Furthermore, maintaining physical functioning related to ADLs can promote independence (Saajanaho et al., 2015). This, in turn, could relieve the burden on nurses and reduce the gap in demand between care and nurses, especially given the current nursing shortage. Exercise interventions in nursing homes are typically conducted twice a week for about 1 hour each session (Cordes et al., 2021a). However, engaging in PA only twice a week for about 45–60 min may not promote residents’ daily PA behaviors and their LSM, and it may not reduce the time they spend sitting in one place: Nursing home residents spend most of their time sitting regardless of whether they participate in group sessions once or twice a week (Auerswald et al., 2020). Thus, the unique contribution of PROGRESS is to combine an exercise intervention with an environmental intervention. We assume that both making changes in the nursing home environment and having residents participate in exercise classes will contribute to residents’ physical functioning, PA, and mobility (Broers et al., 2017; Blaga et al., 2018; Kwan et al., 2020; Hernandez et al., 2023). While the exercise intervention aims to have participants practice certain physical and cognitive functions based on well-known exercise principles, such as intensity and progression, the environmental intervention is particularly aimed at removing obstacles in the environment that residents face. Since this intervention equips the entire nursing home with exercise stations, PROGRESS may reduce nursing home residents’ sedentary behavior and improve their LSM. Further, both types of interventions aim to help residents establish new social contacts. Also, because motivational factors are important determinants of exercise participation and PA, we follow a participatory approach to make sure participants are interested in engaging in these behaviors, overcoming motivation barriers. An additional unique aspect of PROGRESS is its follow-up phase, which will last for 16 weeks after the intervention is completed (after t3, week 37–53). This phase aims to evaluate the program’s sustainability and related changes in primary and secondary outcomes. (Fiatarone et al., 1990; Crocker et al., 2013; Johnen and Schott, 2018; Cordes et al., 2019). It is expected that during the follow-up period, the primary and secondary outcomes will worsen but not return to the baseline level.

This study has several limitations that should be acknowledged. First, while Fitbit trackers were used to objectively assess physical activity, periods with zero recorded steps may not exclusively indicate sedentary behavior but could also reflect times when the device was not worn. Moreover, brief interruptions or incomplete wear periods may have influenced the calculation of total wear days, potentially leading to an underestimation of actual activity levels. Second, the absence of a traditional control group limits the ability to attribute observed effects solely to the interventions, as natural fluctuations in physical activity or contextual factors cannot be ruled out. Third, adherence to the non-guided environmental intervention cannot be systematically controlled. Furthermore, in the case of the guided environmental intervention, only attendance at the supervised sessions can be monitored, but not when the participants practice independently. Nevertheless, we could interview the nursing staff to assess whether these interventions lead to the anticipated increase in mobility. In contrast, the other interventions are supervised, and the use of new devices is guided – an important aspect, as guidance has been shown to be a key factor for PA behavior (Antoniewicz and Brand, 2016).

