**Methods:**

The study employs a cluster-randomized controlled crossover design with four intervention groups. Participants will be randomly assigned to one of four groups: a combined exercise and guided environmental intervention (physical activity-promoting culture), an exercise intervention, a guided environmental intervention, or a non-guided environmental intervention. The exercise intervention involves group-based sessions twice a week, while the environmental intervention focuses on implementing PA into daily routines. The guided environmental intervention is equivalent to the non-guided one but provides additional support two to four times weekly. We aim to recruit at least 120 participants from six nursing homes. Each facility will receive two interventions in a 16-week crossover design (36 weeks in total, including weeks for measurements), followed by a 16-week non-guided environmental intervention (follow-up phase). Primary outcomes include steps per day as an indicator of PA behavior, and the Short Physical Performance Battery (SPPB) to assess physical functioning.

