So far, studies have focused on either group-based physical exercise interventions or environmental interventions. While both intervention models show positive results, exercise interventions primarily promote physical functioning, whereas environmental interventions positively affect physical activity. Therefore, we suggest combining group-based physical exercise interventions with approaches to explicitly increase PA levels. As such, we developed this protocol to offer a new intervention model, namely, a physical activity-promoting culture, which combines both types of interventions: group-based physical exercise classes and environmental interventions. We hypothesize that the physical activity-promoting culture might lead to larger effects on PA behavior and physical functioning in nursing home residents than each intervention alone. Additionally, we expect that, individually, the guided environmental intervention and the exercise intervention will be more effective than the non-guided environmental intervention. Thus, the overall aim of the PROGRESS study is to encourage active participation in social life among nursing home residents and to develop guidelines for health promotion.

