### Trial design

Based on existing research and the physical exercise recommendations mentioned above, this monocentric intervention study is conducted through a controlled cluster-randomized crossover design with four arms. The four interventions are randomly paired and ordered using MATLAB (‘nchoosek’ and ‘randperm’ functions), ensuring that each intervention will be combined with each of the other three interventions once. These six different intervention combinations were then clustered randomized to the nursing homes in the agreed order. In general, the trial design can be divided into an intervention and a follow-up phase with four separate weeks of measurements (t1-t4). So t1 is the baseline measurement time point, t2, with a double role, corresponds to the post-measurement point for the first intervention as well as the pre-measurement point for the second intervention phase. According to this, t3 will be the post-measurement point for the second intervention. 16 weeks after t3, the study will be concluded with the follow-up measurements (t4) after 52 weeks (see Figure 1). The date of first enrollment was August 2022.

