### Non-guided environmental intervention

The non-guided environmental intervention will use the same materials as the guided environmental interventions. However, this intervention will not be supervised or guided, so participants must engage independently, with the assistance of nursing home employees or relatives. This non-guided environmental intervention also serves as the follow-up condition between t3 and t4 (see Table 2).

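### Exercise-only always shares its home with an installed environment, so where it runs second the plan does not protect the exercise-alone contrasts

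*Protocol article*

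**What the plan says.** Trial design in the Protocol article forms all six pairs of the four interventions, "ensuring that each intervention will be combined with each of the other three interventions once", and allocates one pair to each home. The order is random as well: "The four interventions are randomly paired and ordered using MATLAB".

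Table 2 shows that the culture, guided and non-guided interventions share one set of materials: indoor paths, posters, seated bicycles and other equipment, a brochure, an outdoor route booklet from week 9, and a training session for nursing staff beforehand. The section on the non-guided intervention confirms this: "The non-guided environmental intervention will use the same materials as the guided environmental interventions". The Guided environmental intervention section presents the component as a structural change to the building lasting 16 weeks, and the Discussion says of its reach: "Since this intervention equips the entire nursing home with exercise stations". Only the exercise intervention has none of this.

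On timing, "t2, with a double role, corresponds to the post-measurement point for the first intervention", and the same visit is the pre-measurement for the second phase.

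Statistical analysis specifies a 4 × 2 linear mixed model on t1:t2 and t2:t3. It names no period, sequence or carry-over term. The Introduction's main hypothesis is that the "physical activity-promoting culture might lead to larger effects on PA behavior and physical functioning in nursing home residents than each intervention alone". It also expects exercise to do better than the non-guided environment.

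**The concern.** Both hypotheses need a phase that delivers exercise without the environment. Because each of the other three interventions installs the environment, every exercise phase that runs second follows an environmental phase in the same building. If the materials are still there, the residents have roughly exercise plus the non-guided environment. The combined culture then differs from that phase mainly by the guidance. The exercise-versus-non-guided comparison becomes an add-on comparison, because the exercise side contains what it is compared with.

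Staff training and residents' familiarity with the stations cannot be taken back in any case. A non-guided phase that follows the culture or the guided intervention has a related problem: it starts with residents who have already been coached. The trial's conclusion about exercise alone, and about what the combination adds to it, depends on this, yet the limitations in the Discussion do not mention it.

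**Working it through.** The plan gives no figure for this point, so the check covers structure, timing and an illustration of size.

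**Structure.** Four interventions give 4 × 3 / 2 = 6 pairs. Exercise is in three of them, with the culture, the guided and the non-guided intervention. All three partners carry the environmental component (Table 2). So exercise running second always means exercise after an environment.

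**Number of homes affected.** The realised order is not given, so the count is 0, 1, 2 or 3 of 3. Assuming an independent coin flip within each pair, the probabilities are 0.125, 0.375, 0.375 and 0.125. At least one home is affected with probability 1 − 0.125 = 0.875, and the mean is 1.5 homes.

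**Time for washout.** Three 16-week phases and four measurement weeks use 3 × 16 + 4 = 52 of 52 weeks. If t4 falls after week 52, as the Discussion's follow-up range of weeks 37 to 53 allows, the first 36 weeks leave 36 − 32 − 3 = 1 week. Neither count includes a stated washout.

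**Effect on the contrasts.** Let X be the exercise effect, G the guided-environment effect, U the effect of the environment left in place, u = U/G, and q the share of exercise phases that run second. The documents give no value for u or q; the values below are assumptions. Only the exercise side is varied. The intended culture-versus-exercise contrast is (X + G) − X = G.

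- Case A: effects build up within each phase, or post-phase levels are compared. Exercise averages X + qU, and the contrast is G(1 − qu).
- Case B: the environment gives a sustained level shift, change from t2 is analysed, and materials stay. A second-phase exercise change is X + U − G, and the contrast is G(1 + q(1 − u)).
- Case C: as B, but materials are removed. The contrast is G(1 + q).

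Multiples of G:

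| q | u | A | B | C |
|---|---|---|---|---|
| 1/3 | 0.25 | 0.917 | 1.25 | 1.333 |
| 1/3 | 0.5 | 0.833 | 1.167 | 1.333 |
| 1/3 | 1 | 0.667 | 1.0 | 1.333 |
| 1/2 (mean) | 0.25 | 0.875 | 1.375 | 1.5 |
| 1/2 (mean) | 0.5 | 0.75 | 1.25 | 1.5 |
| 1/2 (mean) | 1 | 0.5 | 1.0 | 1.5 |
| 1 | 0.25 | 0.75 | 1.75 | 2 |
| 1 | 0.5 | 0.5 | 1.5 | 2 |
| 1 | 1 | 0 | 1.0 | 2 |

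In case A at q = 1/2, the sample needed for this contrast rises by 1/(1 − qu)²: 1.31, 1.78 and 4.0 times for u = 0.25, 0.5 and 1. Cases B and C treat the preceding environment as guided. Where the partner was non-guided, the prior level is U rather than G, so B adds nothing and C adds less.

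The intended exercise-versus-non-guided contrast is X − U. Case A turns it into X − (1 − q)U, which favours exercise. Case B turns it into X − U − q(G − U), which does the opposite.

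**The case against.** A reader might infer that exercise run second really is exercise plus environment, and that the main contrast is therefore diluted. The documents support neither step.

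No section says the materials stay. The environmental intervention has a 16-week length, Table 2 bounds its parts by week, and the non-guided environment is named as a separate condition for t3 to t4. That fits phase-bound delivery, although it does not establish removal. How posters and bicycles are handled at crossover could sit in a fuller protocol.

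Dilution is only one possible direction. With t2 as the new baseline, a sustained shift is already in the pre-measurement, and the contrast may be unchanged or enlarged (cases B and C). On that reading, removing the materials gives the largest distortion.

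The realised order might leave no exercise phase affected, and the residual share is an assumption. Values of u near 1 also sit badly with the plan's own expectation that guidance matters, and the culture would still differ from exercise with leftovers by its supervised sessions.

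All of this stands, and it limits the claim about what was delivered and in which direction the bias runs. It does not show that the contrast is protected. The pairing makes the exposure unavoidable whenever exercise runs second, there is no washout, the training and coaching persist whatever happens to the materials, and the named model does not address it. What an arm delivers is more than operational detail, because it defines the comparison.

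**Conclusion.** The concern holds in conditional form. As written, the plan does not secure an exercise-alone condition in homes where exercise runs second. The number of such homes is 0 to 3 of 3. Under a coin-flip order, which is an assumption, at least one is affected with probability 87.5%.

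Unless materials are removed, those phases are approximately exercise plus a residual non-guided environment. With removal, staff training and residents' coaching still carry over. The contrasts are then distorted in a direction the documents do not settle. At q = 1/2, and with u from 0.25 to 1, the culture-versus-exercise difference keeps 87.5% down to 50% of its size if effects build up or post-phase levels are compared. It becomes 1.0 to 1.375 times its size if the effect is a sustained shift, change from t2 is analysed and the materials stay. These figures show scale only and are not estimates. The point bears on what the trial can conclude and should be addressed.

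**What to change.** - In Trial design and Table 2, state what happens, or happened, to stations, posters, equipment and booklets at crossover, and report the realised order in each home.
- In Statistical analysis, add a period term and a pre-specified sensitivity analysis restricted to the first period (t1:t2). A period term alone is not enough: it removes a shift common to all arms, not a residual specific to exercise after an environment. With six sequences in six homes, each sequence is seen in one home only, so a carry-over term could not be cleanly separated from that home.
- Report second-period exercise phases separately, labelled as exercise after an environmental intervention, and base any exercise-alone conclusion on homes where exercise ran first.
- List carry-over of the environment among the limitations in the Discussion.

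Taking the materials down is not proposed as the remedy. It leaves training and coaching in place, can enlarge the distortion under a change-from-t2 analysis, and is probably too late, since recruitment of homes ended in the third quarter of 2023.

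The cost is in precision, with no fieldwork. At 10 to 20 residents per home, three exercise homes supply 30 to 60 residents before dropout; one home with exercise first supplies 10 to 20. If exercise ran second in all three, there is no exercise-alone estimate, and the report should say so.

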## Data Availability

The raw data supporting the conclusions of this article will be made available by the authors, without undue reservation.
